#### Advertisement Analysis

Participants revealed a tendency to reduce their SM posts during periods of low moods, with the belief that their SM content might not accurately depict their depressive state. SM platforms such as Facebook use algorithms to direct advertisements to suitable users, leveraging search keywords and previously accessed links. A subset of participants acknowledged the practice of targeted advertising, while a minority reported posting specifically to seek support. In addition, participants acknowledged the existing use of targeted advertising and expressed a preference for its application in mental health care provisioning as opposed to its current use. Individuals experiencing depression tend to conduct searches related to health-related topics, resulting in personalized advertisements that align with their search preferences.

#### Network Analysis

For measuring the network, we will calculate reciprocity, cluster coefficient, and betweenness centrality. This will help understand the user’s close connections and how frequently they communicate with them. To analyze the post-centric and user-centric behavior in detail, we need to calculate reciprocity, prestige ratio, clustering coefficient, degree centrality, closeness centrality, betweenness centrality, and eigenvector centrality.

In terms of analyzing the network, we will consider “u” as the user whose network property we will analyze. A node indicates a person, and an edge is considered a connection or link. Reciprocity will reflect how often “u” has responded to any message.

The prestige ratio indicates the bidirectional communication of the user. That means after texting back to any message, it tracks the number of times they have participated and the frequency of their interactions.

Mathematically, the reciprocity formula is as follows:

Reciprocity = (number of reciprocated connections) / (total number of connections) **(5)**

To calculate the reciprocity, we have to count the number of connections between pairs of users in a network and determine how many of these connections are reciprocated. A reciprocated connection occurs when 2 nodes have a mutual connection with each other. For example, if user A is connected to user B and user B is also connected to user A, it is considered a reciprocated connection. A higher reciprocity score in network analysis indicates a more tightly connected and interactive network with stronger bidirectional relationships between users.

Clustering coefficient measures how likely it is for the friends or connections of a user to be friends or connected to each other. Basically, it provides a quantifiable measure of how much users tend to form groups or clusters within the network.

For user i, who has ni neighbors, the clustering coefficient Ci is defined as the ratio of ei connected pairs to the number of all possible connections among the ni neighbors:

Ci = 2ei / (ni([ni – 1]) **(6)**

The formula calculates the clustering coefficient by dividing the number of actual connections between the neighbors of the user i (2ei) by the number of possible connections between the neighbors of the user i (ni([ni–1]).

A higher clustering coefficient score in SM analysis signifies a network with well-connected subgroups or clusters, indicating the presence of close relationships and social interactions among users within these groups. A lower clustering coefficient score in social network analysis indicates a network with less local interconnectedness and fewer cohesive groups, suggesting a more diverse and less tightly knit social structure among the nodes.

Closeness centrality annotates how easily “u” can reach other users in a community. To be more specific, it measures how close or directly connected a user is to other users. A high closeness centrality indicates that “u” is closely connected to many other users. A low closeness centrality indicates that “u” is distant from others in the network. It means “u” may need to go through multiple intermediate connections to reach other users.

Closeness centrality, as the name suggests, is an index defined in terms of distance. Length of a (s, r) path represents the number of edges contained in it. We define the (shortest path) distance, dist (s, r) of s, r∈V as the minimum length of any (s, r) path. We reiterate that we consider only connected graphs for now and observe that dist (s, s)=0 for all s ∈ V. The distance matrix D=(dist[s, r])s, r∈V of an undirected graph is symmetrical, so the total distance, dist(v), of a vertex v ∈ V is obtained as either the row or column sum:

**(7)**

Because of this reversal in ranking, the closeness centrality of a vertex s ∈ V is usually defined as the inverse of the total (or, equivalently, average) distance [49]

[figure not shown]

**(8)**

Higher closeness centrality indicates that a user is more central and well connected in the network, while lower closeness centrality suggests that a node is less central and may have less efficient access to other nodes.

Betweenness centrality is a widely used measure that captures a user’s role in allowing information to pass from one part of the network to another. It shows the potential of a user in terms of communication:

[figure not shown]

**(9)**

The number of shortest paths from a vertex i to a vertex j that goes through a vertex k, denoted sp_ij_ (k), is the maximum number of shortest paths from vertex i to vertex k in the shortest path tree rooted at i and the number of shortest paths from vertex j to vertex k in the shortest path tree rooted at the vertex j [93].

Users with higher betweenness centrality have more control over the flow of communication in the network and act as important mediators or connectors between different parts of the network. In contrast, users with lower betweenness centrality have less influence over the overall communication patterns and may be more localized in their interactions. Betweenness centrality is a measure of a user’s importance in facilitating communication, and it provides insights into the user’s role in maintaining network connectivity and communication.

One of the potential concerns of this study is addressing the data imbalance challenge, particularly regarding the occurrence of suicide. To mitigate this imbalance, we have studied the techniques that were previously implemented in similar settings. Firstly, we will use appropriate data preprocessing techniques, such as oversampling or undersampling methods, based on the collected data to ensure that the predictive model is trained on a balanced data set. In addition, feature selection methods will be used to prioritize the most informative variables related to depression and suicide prediction, thereby minimizing the impact of data skewness on the model’s performance. Furthermore, we will consider the use of robust evaluation metrics, such as precision, recall, and *F*_1_-score, which will allow for a comprehensive assessment of the model’s predictive capability across different outcome classes, effectively addressing the challenge posed by data imbalance. These approaches would provide valuable insights into addressing data imbalance challenges in predictive modeling studies related to mental health.

### Evaluation Metric

#### Overview

In the process of evaluating our models, we will use various ML metrics that offer critical insights into their performance. These metrics play a pivotal role in determining the accuracy and efficacy of the models. Specifically, we will be focusing on the following metrics [48]: true positive, false negative, true negative, and false positive. These metrics hold significance in assessing the predictive capability of the models in a classification context.

#### Sensitivity (True Positive Rate or Recall)

This metric measures the ability of the model to correctly identify people who are depressed. It calculates the ratio of true positives (correctly identified people who are depressed) to the sum of true positives and false negatives (people who are depressed incorrectly classified as people who are not depressed).

#### Specificity (True Negative Rate)

This metric evaluates the proportion of actual negatives (people who are depressed) that are correctly identified as such. It measures the accuracy of identifying healthy individuals who do not have depression.

#### Precision (Positive Predictive Value)

Precision calculates the fraction of relevant instances (positively labeled) among the predicted instances. It provides an assessment of the accuracy of positive predictions made by the model:

TP / (TP + FP) **(10)**

#### F1-Score

The *F*_1_-score is a measure that combines precision and sensitivity (or recall) into a single metric. It calculates the harmonic mean of precision and sensitivity and is particularly useful when dealing with imbalanced data:

(2* precision score × recall score) **/** (precision score + recall score) **(11)**

#### Accuracy

Accuracy represents the overall performance of the model, measuring the proportion of correctly classified instances out of the total instances. The error rate, which complements accuracy, quantifies the proportion of misclassified instances:

(TP + TN) / (TP + TN + FP + FN) **(12)**

#### Evolution

Among the array of standard evaluation metrics, precision, recall, and *F*_1_-score are given more weightage to assess the efficacy of models in accurately classifying depression classes. When assessing early detection algorithms, it is crucial to consider not only the accuracy of decisions but also the associated delays. In line with this, Wang and Mark [48] introduced the early risk detection error metric, which penalizes untimely correct decisions to address this concern. Flatency, introduced in the CLEF eRisk 2021 [59], is an interpretive evaluation metric proposed alongside the early risk detection error metric to enhance interpretability [30]. In addition, known as latency-weighted *F*_1_, flatency combines *F*_1_-score with speed, reflecting both accuracy and efficiency in identifying users’ content, particularly emphasizing early and accurate classification. By considering these metrics, we can gain a comprehensive understanding of the performance of our models in terms of their ability to correctly identify individuals who are depressed and individuals who are not depressed. The streamlined flow of the depression identification system is depicted in Figure 2.

**Figure 2 figure2:**

Deployment of the suicide ideation prediction model based on the 9-item Patient Health Questionnaire (PHQ-9) and Facebook data examination. ML: machine learning; NLP: natural language processing.

## Results

Our system is anticipated to automatically detect posts related to depression by analyzing the text and use pattern of the individual with the best accuracy possible. Ultimately, our research aims to have practical utility in identifying individuals who may be at risk of depression or in need of mental health support.

Simultaneously, by analyzing daily activities on SM, we aim to determine how frequently individuals write “negative” posts on Facebook, as such posts are often associated with depression [94]. Additionally, we will examine the types of emojis that are used repeatedly by these individuals. This will help us identify how often an individual uses emojis while writing a post. Moreover, if a person does not use an emoji, their posts will be detected based on the score of their “negative” emotional words (ie, “sad,” “angry,” or “fear”).

By accurately classifying individuals based on their text analysis, we hope to contribute to the development of early detection systems or interventions that can enhance mental health screening and well-being.

## Discussion

### Overview

In this study, we will focus on the South Asian region, mainly Bangladesh and India, which is still dealing with economic issues and some problems with regard to basic rights. People from this region do not pay adequate attention to mental health and well-being. Therefore, we aim to build such a solution that will cover most of the gaps regarding all the mentioned facts. Our goal is to establish a procedure that will analyze how a collection of behavioral indicators that appear on SM may be used to forecast postings that are suggestive of depression and, in turn, comprehend widespread suicidal tendencies in populations.

### Principal Findings

Our study will begin by administering basic questions to users, followed by a filtering process to select suitable participants for our study. Upon obtaining the Facebook data, our analysis will commence. We will initially determine whether Facebook serves as the primary SM platform for the participants, a crucial factor influencing the accuracy of our predictions. In case it is their main platform, we will focus on their interactions, encompassing messages, posts, comments, and gaming activities. Our analysis will extend to anonymous actions and their engagement with content related to depression.

Conversely, in instances where Facebook is not the predominant medium, judicious focus is shifted to the advertisement analysis model. This model hinges on deciphering users’ web-based behavior, scrutinizing their browsing history, visited sites, and thematic inclinations, particularly within realms such as consultancy or support services. For participants who primarily use other platforms, our analysis will shift to evaluating the types of websites they frequent and the content they engage with. This system will work privately to assess the risks associated with anticipated changes in the future while taking into account metrics related to SM activity. We aim to demonstrate a significant correlation among Facebook games, user profile information, and content such as advertisements on mental health as depicted in Textbox 1.

Finally, we will incorporate an assessment of the frequency of their posting, commenting, friend engagement, and previous questionnaire responses, thus enhancing the depth and accuracy of our predictive model. Our ultimate prediction will amalgamate these distinct analyses through advanced techniques. Informed by the outcome of these individual models, our predictive synthesis advances, culminating in a definitive assessment of the presence or absence of suicidal ideation.

Consideration of data variables for suicidal ideation detection based on Facebook activity status.If a user is active on Facebook9-item Patient Health Questionnaire (PHQ-9) scoreFacebook games analysisBio analysisPost and comment analysis with or without the user’s nameNotification analysisKinds of groups joined and pages liked analysisSearch history analysisAdvertisement analysisDiurnal activity valueNetwork attributes calculation

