We aim to build an automatic system to analyze posts and engagement on SM and predict the person’s behavior and mental state. Moreover, we will use the 9-item Patient Health Questionnaire (PHQ-9) as a validated and reliable patient self-report measure to assess depression [25-27]. We will focus on the interaction and participation of people on SM, which will clearly indicate their interest in communicating their tendencies with others, and text pattern analysis, which will show their emotional state. Most studies have analyzed public account data, but we will also analyze some private account data with users’ consent. We are focusing on some unexplored and unique variables, such as studying engagement with Facebook games and advertisements, analyzing the content of anonymous posts, and establishing a correlation between them and depressive symptoms. In addition, we focus on analyzing data on people from South Asian countries because very few works have been done targeting this region. Moreover, we will ensure the efficiency and usefulness of the model, which we will assess by examining a group of people. In addition, the model will function as a screening tool and symptom-tracking tool, enabling comprehensive assessments of suicidal thoughts, depression severity, and treatment progress as depicted in the Figure 1 [28].

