## Methods

Our procedure will consist of several key steps. These are data collection and preparation, feature engineering, model selection, model training, model evaluation, prediction, and model deployment.

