### Limitations

However, this study may have a few limitations and biases that are crucial to consider. First, the recruitment of participants through web-based platforms may introduce selection bias, as individuals who are active on SM may be different from the general population [97]. In addition, reliance on self-reported data, such as responses to demographic questions and mental health assessments, may introduce response and social desirability biases. Participants may underreport sensitive information or provide socially acceptable responses, leading to inaccuracies in the data collected [98]. Moreover, the interpretation of textual data, including language nuances and sentiment analysis, is subject to inherent biases in NLP algorithms [99]. Future research should aim to mitigate these challenges through methodological refinements and validation studies.

Future research directions can include comprehensive validation studies that directly compare the outcomes of our screening method with those of clinical assessments conducted by mental health professionals. This validation process would involve recruiting control groups and conducting direct comparisons to assess the accuracy and reliability of our screening results in identifying individuals with suicidal ideation. This will provide valuable insights into the strengths and limitations of our approach. By establishing the concordance between our screening results and clinical diagnoses, we can enhance the credibility and utility of our screening methodology in real-world settings [100]. Researchers can also conduct a broader exploration of alternative screening methods and interventions based on the screening results. Incorporating additional data sources or using advanced ML techniques could enhance accuracy and efficiency. In addition, developing targeted interventions based on the screening results holds promise for improving mental health outcomes and preventing suicide [101].

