### Conclusions

The study’s timeline unfolds as follows. The data collection, which includes recruiting participants, conducting surveys, and gathering Facebook data, is scheduled to conclude by November 2024. Anticipating the system’s ability to accurately detect signs of depression in text and use patterns, we aim to advance early detection systems or interventions, completing the ML model by January 2025. The final results are expected to be available in February 2025.

By delving into these multifaceted aspects, this study will offer a comprehensive and pioneering approach to the field of mental health. Our approach to predicting depression through SM activity, or the examination, is not intended to replace conventional surveillance systems or laboratory-based depression diagnoses. To maximize the advantages of these approaches and concepts and improve people’s quality of life, we believe it is important to highlight the possibilities. This will also encourage discussion and raise awareness of any potential issues that should be resolved on individual and societal levels.

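### The design cannot support a definitive call on suicidal ideation: its only reference is a self-report scale that is also a model input, and clinical comparison is left to later research

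*Protocol article*

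**What the plan says.** Four places in the protocol article describe what the model will deliver:

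- **Discussion, Principal Findings:** the component analyses are combined, "culminating in a definitive assessment of the presence or absence of suicidal ideation".
- **Methods, opening paragraph:** the steps of the procedure end with "model training, model evaluation, prediction, and model deployment".
- **Figure 2 caption:** "Deployment of the suicide ideation prediction model based on the 9-item Patient Health Questionnaire (PHQ-9) and Facebook data examination".
- **Introduction, Background:** "the model will function as a screening tool and symptom-tracking tool".

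Two places limit it:

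- **Discussion, Limitations:** "Future research directions can include comprehensive validation studies that directly compare the outcomes of our screening method with those of clinical assessments". The same section warns that self-reported mental health assessments may be distorted by underreporting.
- **Discussion, Conclusions:** the approach "is not intended to replace conventional surveillance systems or laboratory-based depression diagnoses".

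The reference measure is described under Data Collection and Clinical Assessment. It is the PHQ-9, completed on the study website and used to validate the Facebook-based result.

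**The concern.** A definitive statement that suicidal ideation is present or absent needs a reference that establishes ideation, is independent of the model, and is used to measure accuracy for that outcome. The article gives the claim but not these conditions, and its own Limitations section places the missing comparison outside the study. At stake is what the results can be taken to mean. Good agreement with a questionnaire could be reported as the ability to establish or rule out suicidal ideation, and deployment could be read as following from that agreement. For this outcome a wrong call of absence is the more serious error, and the study has no means of estimating how often it occurs against a clinical standard.

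**Working it through.** The plan states no figure to reproduce here, so the check sets the sections side by side and asks what the design can establish.

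**1. What is the reference?** Data Collection and Clinical Assessment name the PHQ-9 and nothing else. The Background calls it a self-report measure. ML Modeling mentions people with diagnosed depression but names no source for the diagnosis. Clinical Assessment says the ninth item bears on suicidal thoughts, but does not name it as the outcome label.

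**2. Is the reference free of acknowledged error?** No. Limitations says participants may underreport. A person with ideation who denies it on the PHQ-9 would count as a true negative if the model also says absent. The study cannot see such an error.

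**3. Is the reference independent of the model?** Not as written. Data Collection treats the PHQ-9 as the yardstick for a result predicted from Facebook data. Textbox 1 lists the PHQ-9 score as an input for active and inactive users alike, and for inactive users it is one of only two inputs. Principal Findings also feeds earlier questionnaire responses into the final prediction. The overlap depends on the label:

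- If the label is a PHQ-9 severity band, the score determines it completely.
- If the label is item 9, the score contains it. Clinical Assessment gives nine questions and a range of 0 to 27. Assuming equally scored items, each contributes up to 27 / 9 = 3 points, and the other eight up to 8 × 3 = 24. A total of 25 or more then guarantees a non-zero item 9, and a total of 0 guarantees a zero. Between those values the score is informative about item 9 by construction.

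In either case, part of the measured agreement is built in.

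**4. Do the metrics address suicidal ideation?** The Sensitivity and Specificity sections define their classes by depression, and the Evolution section weights precision, recall and F1 for classifying depression. No accuracy measure is defined for ideation, although ML Modeling speaks of predicting suicide risk.

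**5. Is there a check against clinical assessment?** Not in this study. The Limitations section names "comprehensive validation studies that directly compare the outcomes of our screening method with those of clinical assessments conducted by mental health professionals" as future work, and says that this work would assess accuracy and reliability in identifying people with suicidal ideation.

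**6. What stands before deployment?** The Methods list puts model evaluation before prediction and deployment. ML Modeling gives a 7:3 split of one data set and a choice of the most effective model. No section makes deployment depend on the deferred comparison.

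Steps 1 to 5 leave the study able to estimate agreement with self-reported PHQ-9 status, provided the overlap in step 3 is removed. They do not allow a definitive assessment of suicidal ideation.

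**The case against.** The strongest reply is that this is largely wording. Principal Findings also calls the output a prediction, so definitive may mean only the final binary classification. The Conclusions section disclaims replacing conventional diagnosis, Limitations asks for clinical validation, and a screening aim is compatible with both. Some evaluation is planned first: the Methods list includes it, the Evaluation Metric section describes it, and the Background promises to assess usefulness by examining a group of people.

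Much of this stands. It would be wrong to say that nothing precedes deployment, and the remedy is mostly textual. But the disclaimer concerns surveillance and depression diagnosis and leaves the claim about ideation uncorrected. The Background promise names no reference standard. None of the planned evaluation uses an independent clinical reference for ideation.

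A reader might go further and infer that participants will be told they do or do not have suicidal ideation, and so be falsely reassured or alarmed. The article does not support that. It describes data being uploaded and analysed, with no return of individual results. The timeline in Conclusions runs to model completion and final results with no deployment period, and the content of Figure 2 is not available. Release and feedback arrangements may also sit in a fuller protocol.

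Nor can missed cases be counted by applying an assumed prevalence and accuracy to the recruitment target of 300 + 300 = 600 to 1500 + 700 = 2200 people. Those people supply the model's data and are not users of a deployed tool. The Participants section plans a balance of positive and negative samples, so natural prevalence need not apply to them.

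**Conclusion.** The point holds as a mismatch between claim and design. The article promises a definitive call on the presence or absence of suicidal ideation and lists deployment. Its only reference is a self-report scale that it admits may be underreported and also uses as an input, its sensitivity and specificity definitions concern depression, and it defers the clinical comparison.

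The size is qualitative. No sensitivity, specificity, prevalence or precision target for suicidal ideation is stated, so no count of errors or predictive value can be derived. The conclusion rests on reading Textbox 1 as a list of model inputs, which is how it is captioned, and on the PHQ-9 being the only reference, since no other is named. It does not depend on what deployment means in practice or on whether results reach participants.

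**What to change.** - **Principal Findings:** replace the definitive assessment with a provisional prediction of self-reported PHQ-9 status, stating which PHQ-9 quantity is the label.
- **Principal Findings and Textbox 1:** remove the PHQ-9 score and all its items from the predictors whenever the PHQ-9 is the label. Without this, the reworded claim would still be partly circular.
- **Methods opening and Figure 2:** end this study at offline evaluation, and state that deployment depends on the comparison with mental health professionals' assessments described in Limitations.
- **Background:** restate the screening and symptom-tracking role as a later aim.

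The cost is mainly wording, one step taken out of the study flow, and one input dropped from the model. Inactive users would then be left with advertisement content alone. The downside is a more modest claim and later practical use.
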